#### Salvage procedure

Salvage procedures and adverse events will be reported descriptively. Reoperation in the form of hardware removal will be classified as a complication, not a salvage procedure. There will be two analyses for ITT: one including salvage procedures and one excluding them. The timing of salvage procedures will be analyzed using a Cox proportional hazards model to compare time to salvage between treatment groups.

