#### Treatment failure

In case of treatment failure in either group, defined as persistent pain or a failed osteosynthesis, a salvage procedure with secondary osteosynthesis, including the possibility to use a locking plate with a graft or a reverse shoulder arthroplasty (RSA), will be offered. The decision to proceed to a salvage procedure will be made in collaboration with the patient and the surgeon. Failed osteosynthesis and the most appropriate salvage procedure will be defined by the surgeon.

Cross-over to RSA or revision osteosynthesis is considered a failure of treatment regardless of group allocation. The patient will remain in the study. The reason for crossing over will be noted and reported.

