#### Conversion to surgery

The criteria for conversion to surgery are based on an overall clinical evaluation conducted in collaboration with the patient. In the non-surgical group, the primary reason for conversion is persistent severe pain after 6–12 weeks. In the surgery group, adverse events can serve as reasons for conversion to RSA. Patients who discontinue for reasons unrelated to surgery will be documented and recorded. Patients receiving osteosynthesis or RSA will also have follow-up assessments after 6, 12, and 24 months.

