### Statistical analysis

The statistical analysis plan is available within Supplementary Information, file 2.

Baseline characteristics will be presented using descriptive statistics. We will compare the following patient characteristics between the groups at baseline: age (categorized into 5-year age groups), sex, height, weight, ASA score, fracture classification (Neer [5]), dominant arm (yes/no), smoking, alcohol consumption, educational level, working status, work type, osteoporosis (three-level ordinal variable based on *T*-scores (osteoporosis, osteopenia, and normal bone density)), and clinical frailty scale [36]. SD will be reported, and *n* (%) for categorical values.

Osteoporosis will be collected and reported descriptively as a three-level ordinal variable based on *T*-scores (osteoporosis, osteopenia, and normal bone density).

The OSS results for surgical and non-surgical treatment groups at 6, 12, and 24 months will be tabulated and graphically represented with mean, SD, median and IQR according to the distribution.

The primary outcome, OSS at 12 months, will be analyzed using two-sample *t*-test comparing the two treatment groups. Normality assumptions will be assessed, and if violated, alternative methods such as transformation or non-parametric Mann–Whitney *U* test will be considered. As suggested in the extension of the CONSORT 2010 statement, the primary outcome will be analyzed for the intention-to-treat (ITT) population.

In addition, linear mixed models will be used to analyze OSS and EQ-5D over time (6, 12, and 24 months) accounting for the repeated measures structure and to explore outcome trajectories. Model-based contrasts from the LMM will be used to estimate adjusted between-group differences at specific time points. Missing data will be handled within the mixed model framework, assuming data are missing at random. Details are provided in Supplementary Information, file 2.

We will record and report adverse events in each group. At the 6-month follow-up, patients will be asked, and we will record and report the length of rehabilitation in municipalities (in weeks) and whether the patient has followed the rehabilitation plan.

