### Protocol violation

Patients who drop out of the trial will be noted, along with the reasons. The patients will remain in the study and be included in the ITT analysis. Numbers and time for loss to follow-up will be reported.

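### One of the two analyses labelled ITT excludes salvage procedures: it is not ITT, it favours the arm with more failures, and the article does not say which of the two is primary

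*Protocol article*

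**What the plan says.** The Statistical analysis section fixes outcome and test ("The primary outcome, OSS at 12 months, will be analyzed using two-sample" t-test) and population: "the primary outcome will be analyzed for the intention-to-treat (ITT) population". The Salvage procedure section then adds: "There will be two analyses for ITT: one including salvage procedures and one excluding them". It does not name the outcome, rank the two analyses, or call either one supplementary or a sensitivity analysis.

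The Treatment failure section shows what salvage is: "In case of treatment failure in either group, defined as persistent pain or a failed osteosynthesis, a salvage procedure" is to be offered. It also says: "Cross-over to RSA or revision osteosynthesis is considered a failure of treatment regardless of group allocation. The patient will remain in the study". The decision is shared by patient and surgeon, neither of whom is blinded. The Conversion to surgery section gives arm-specific triggers: "In the non-surgical group, the primary reason for conversion is persistent severe pain after 6–12 weeks". In the surgical arm, adverse events can lead to conversion to reverse shoulder arthroplasty.

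**The concern.** ITT means that patients are analysed as randomised, whatever happened afterwards. Salvage happens afterwards and is the trial's own marker of failure. Excluding it removes patients who did badly. The reasons for removal differ by arm (pain after non-surgical care, adverse events after fixation), so the numbers removed may differ too. The remaining groups are no longer protected by randomisation, and the arm that loses more failures looks better than it was. Pain is also one component of the OSS, so the non-surgical trigger is related to the outcome scale itself.

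Because both analyses carry the ITT label without a ranking, the article leaves open which result answers the primary question if the two disagree.

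**Working it through.** **The plan's own figure.** Inputs from the sample size section: difference 9.6, SD 12, power 80%, significance level 5% (taken as two-sided).

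n per group = 2 × (1.960 + 0.842)² × (12/9.6)² = 2 × 7.85 × 1.5625 = 24.5, so 25. Allowing for 15% loss, 25/0.85 = 29.4, so 30. Both stated figures reproduce, and the sample size is not in dispute.

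**Assumptions.** The article gives no salvage rates by arm. I take 5% to 30%; the upper end borrows the failure rate at which the data monitoring committee would reconsider inclusion. Salvage falls on the lowest fraction p of a latent recovery variable that has correlation ρ with 12-month OSS. I use ρ = 0.3 to 0.8, because salvage is decided months before the score is taken and may itself change that score.

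**Formula.** Removing the lowest fraction p raises an arm's mean by ρ × SD × φ(z_p)/(1 − p). At SD 12 and ρ = 1:

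| p | shift in points |
|---|---|
| 5% | 1.30 |
| 10% | 2.34 |
| 20% | 4.20 |
| 30% | 5.96 |

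The bias in the between-group difference is the gap between the two arms' shifts, multiplied by ρ. With no true effect:

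| Salvage rates | gap at ρ = 1 | ρ = 0.3 | ρ = 0.5 | ρ = 0.8 |
|---|---|---|---|---|
| 20% vs 10% | 4.20 − 2.34 = 1.86 | 0.6 | 0.9 | 1.5 |
| 30% vs 5% | 5.96 − 1.30 = 4.66 | 1.4 | 2.3 | 3.7 |
| equal rates, same selection | 0 | 0 | 0 | 0 |

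The bias favours the arm with more salvage. The largest value, 3.7, is 3.7/9.6 = 39% of the target difference.

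**Simulation check** (20,000 runs, 25 analysed per arm, same model). With no true effect and 5% surgical versus 30% non-surgical salvage, the estimate shifts by 1.40, 2.34 and 3.71 points towards non-surgical treatment at ρ = 0.3, 0.5 and 0.8, which matches the formula. With a true difference of 9.6 and the same rates, the excluding analysis estimates 8.2, 7.3 and 5.9. With 20% surgical versus 5% non-surgical salvage it overestimates instead, at 10.5 to 11.9. Keeping all patients as allocated returns 9.6 throughout, with type I error of about 5%.

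**The two readings of the exclusion.** It may mean dropping salvaged patients, or dropping only data collected after salvage. For a t-test on 12-month OSS, a patient salvaged before month 12 is lost under either reading. The readings differ only for salvage after month 12. Neither is an ITT analysis.

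**The case against.** The strongest reply is that the primary analysis is already identifiable. The Statistical analysis section assigns the primary outcome to ITT, and the Treatment failure section keeps patients who cross over in the study. Together these point to the version that includes salvage. The two-analyses sentence sits under its own heading and never calls the excluding version primary, and the unseen analysis plan may rank them. This largely stands. A reader might infer that the trial has two rival primary analyses, either of which could be presented as the answer. The text does not go that far: both analyses are pre-specified, salvage is also compared between arms over time, and two abstracts are to be written before unblinding. What remains is that the article itself gives the ITT label to an analysis that is not ITT, and no ranking elsewhere makes that label right.

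A reader might also infer biases of 1.9 or 4.7 points. Those need ρ = 1, meaning that salvaged patients are exactly the lowest scorers at 12 months. The documents do not support this: non-surgical conversion is mainly for pain after 6–12 weeks, and OSS is measured later, after the salvage procedure.

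Nor does a single figure for lost power follow. Excluding patients reduces n, but trimming the lower tail also reduces the SD. With 30% salvage in both arms and a true difference of 9.6, simulated power runs from 65% (ρ = 0.3) to 79% (ρ = 0.8). It would matter for the trial only if the excluding analysis were primary.

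Finally, the rule in the Protocol violation section, "The patients will remain in the study and be included in the ITT analysis", concerns patients who drop out. It shows the article's general intent but does not settle how salvage is handled.

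**Conclusion.** The point holds as a mislabelled analysis and an unstated ranking. The excluding version conditions on a post-randomisation failure with arm-specific triggers, so it is not ITT under either reading. It is biased towards the arm with more failures, provided that salvaged patients tend to score below average at 12 months.

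The size is conditional: about 0.6 to 1.5 OSS points at 20% versus 10% salvage and 1.4 to 3.7 points at 30% versus 5%, with SD 12, no true effect and ρ from 0.3 to 0.8. It is near zero if both arms fail equally often and for patients with similar prognosis. The direction cannot be known in advance, because the article gives no salvage rates. The planned sample size and the analysis of all randomised patients are unaffected.

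**What to change.** 1. State that the single primary analysis compares all randomised patients as allocated, using 12-month OSS regardless of any salvage procedure.
2. Delete the excluding version, or relabel it as supplementary and not ITT. If it is kept, say whether patients or post-salvage data are excluded, and what question it answers.
3. Preferably replace it with a supplementary composite analysis that keeps every salvaged patient as an unfavourable outcome, for example by assigning the worst rank and comparing arms with the Mann–Whitney test that the article already names. It should stay supplementary, because salvage decisions are unblinded.

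Carrying forward a pre-salvage OSS is not a workable alternative. Table 1 first collects OSS at 6 months, whereas non-surgical conversion is expected mainly after 6–12 weeks, so many salvaged patients would have no value to carry forward.

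The cost is a wording change in the article and matching text in the analysis plan, plus one supplementary analysis. No new data or patients are needed. The change should be made before any results by arm are seen.

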#### Non-randomized cohort

Patients who declined randomization but consented to follow-up will form the non-randomized cohort. Baseline characteristics will be summarized descriptively and compared between the randomized and non-randomized cohorts, as well as among the non-randomized patients by treatment choice. The primary outcome (OSS at 12 months) will be analyzed by treatment modality. Secondary outcome measures (OSS and EQ-5D) will be presented descriptively and graphically at 6, 12, and 24 months. Analyses will include multivariable linear regression adjusted for baseline covariates; propensity score methods may be applied. The incidence and timing of salvage procedures will be described and analyzed using Cox proportional hazards models.

#### Blinded data interpretation

Although patients and investigators are not blinded to treatment allocation, the primary investigator will conduct blinded statistical analysis through data anonymization and will be supervised by a biostatistician. The OSS and EQ-5D-3L will be completed just before the 6-month visit, collected automatically through REDCap, and will not be reviewed by the investigator prior to analysis. After the blinded statistical analysis has been completed, two abstracts will be written based on the pre-blinding analysis results before the blinding is revealed.

Data will be analyzed using the statistical “R” [37].

#### Interim analyses

An interim analysis will be conducted when 50% (*n* = 30) of the randomized patients have completed their 6-month follow-up, focusing on OSS, failure to treatment, and serious complications. A third party will blind the data to treatment location before analysis. Regardless of whether the interim analyses suggest that the study is unlikely to achieve its primary objectives, the study will proceed as initially planned.

A DMC has been organized to monitor and evaluate the data from the interim analysis. The DMC consists of five independent members: two orthopedic researchers and an orthopedic nurse from Denmark, and one orthopedic researchers and one orthopedic nurse from Finland. All members have equal standing within the committee.

The DMC will monitor unexpected, unwanted events; continued inclusion will be considered if the failure rate is above 30%. Intervention-related hospitalization or mortality will be reported to the ethics committee.

### Data management

All study data will be collected and stored in Research Electronic Data Capture (REDCap) [23]. Clinical assessments and radiographs will be entered directly into REDCap by the investigators (LH, SB, AL, BS, or LK). Questionnaires at 12 and 24 months will be distributed electronically through REDCap. Data will be stored securely on institutional servers with access restricted to study personnel.

### Protocol violation

Patients who drop out of the trial will be noted, along with the reasons. The patients will remain in the study and be included in the ITT analysis. Numbers and time for loss to follow-up will be reported.

### Patient and public involvement

Four patients read and commented on the written information sheet, confirming the understandability and that it was sufficiently informative.

## Discussion

### Relevance of age in existing evidence

Current high-quality evidence on proximal humerus fracture treatment primarily concerns patients from 60 or above. This leaves a knowledge gap in the younger, still working-age population aged 50–65. A Cochrane review reported high- or moderate-certainty evidence that surgery, compared to non-surgical treatment after a displaced proximal humerus fracture, did not provide a better outcome after 1 and 2 years [7]. However, patients aged 50–65 may differ in functional demands, health status, and recovery expectations. Despite this, they are typically underrepresented in clinical trials.

The young shoulder CARE trial was designed to contribute to addressing this evidence gap. By focusing exclusively on patients aged 50–65, the trial aims to generate age-specific data to inform clinical decision-making for this population better. The pragmatic design was chosen to reflect real-world clinical practice and increase external validity.

### Choosing the age range

The age of 50 was chosen because PHF is uncommon in patients under 50, but its incidence increases significantly after this age [1, 2]. Over 80% of fractures occur in patients aged 50 or older [6]. Additionally, at Zealand University Hospital, patients aged 50 and older are routinely referred to a Fracture Liaison Service (FLS) for bone health assessment, supporting the choice of 50 years as a meaningful lower age limit for inclusion.

There is no universally agreed-upon age cut-off for what constitutes an “older” adult, yet age definitions are crucial in trial inclusion and generalizability. The WHO previously characterized older people as those over 65 years (2010 report), the latest age report has no precise definition. The term “older” is too complex due to multiple factors and variations in global age distribution, making it challenging to establish an age cutoff [38]. The Danish Health Authority [39] and International Population Report of the National Institutes of Health [40] define “older” as individuals surpassing the age of 65. In orthopedic research, Sabharwal found that age 65 is the most common age at which a person is considered “older” [41].

We aimed to investigate a population that differs from older adults in terms of functional demands, general health status, and expectations for recovery. To ensure the inclusion of individuals who are still active in the workforce, we focused on patients below the typical retirement age. In Finland and Denmark, the retirement age is 65–67 years [42, 43]. Consequently, we selected 65 years as the upper age limit to target a relatively younger and more active patient group. This allows our trial to clearly complement and extend existing evidence focused on older adults.

### MCID

Currently, an MCID for the OSS in patients with PHF has not been determined. In other shoulder conditions, the MCID for the OSS (ranging from 0 to 48) has been reported to be between 5 and 6.9 [35]. Nonetheless, the concept of MCID is inherently context-dependent and can vary based on factors such as age, sex, baseline functional status, injury mechanism, and comorbidities, and may also evolve over time [44]. Consequently, the MCID should not be regarded as a universal fixed value. In the absence of a PHF-specific MCID, this study adopted a difference of 9.6 points on the OSS—equivalent to 20% of the scale—as a clinically meaningful threshold. This decision informed the sample size calculation, under the premise that surgical intervention should produce a substantial benefit to be deemed appropriate. Future investigations should focus on validating or refining the MCID specific to PHFs.

### Limitations

Several considerations should be noted when interpreting the results of this study. First, only two centers were included, which may limit the generalizability of the findings to broader populations. This choice was deliberate, prioritizing centers where we could ensure complete follow-up and standardized screening of all eligible patients, allowing for consistent and reliable inclusion of the target population.

Second, the sample size is relatively small, and the study was not blinded, which is inherent in surgical trials, as both the surgeon and the patient are aware of the treatment received. To minimize bias related to outcome assessment, we chose patient-reported outcome measures (OSS), allowing patients to evaluate their own shoulder function directly. This approach avoids potential observer bias associated with surgeon-administered instruments.

Despite these limitations, the trial provides valuable age-specific data on patients aged 50–65, a group underrepresented in previous studies. These findings may inform future clinical decision-making and help refine treatment guidelines for displaced proximal humerus fractures in this intermediate age group, particularly regarding the choice between surgical and non-surgical management.

## Data Availability

Data sharing is not applicable to this article as no datasets were generated or analyzed during the current study. The Data Protection Agency of Region Zealand has approved the handling of personal data (p-2024–16591). Compliance with the General Data Protection Regulation (GDPR) and the Danish Data Protection Act will be ensured at all times. A data processing agreement has been signed in both recruiting centers. Research data is stored on REDCap, a secure online patient management program, accessible only to LH, SB, AL, BS, and LK on a secure server at Region Zealand University Hospital (with two-factor authentication login). The primary investigator will have access to the final data set. The REDCap setup ensures that randomization is only possible, if all baseline information is entered correctly. All data will be fully anonymized before publication. The trial results will be published in an open-access peer-reviewed journal.

## Abbreviations

ASA: American Society of Anesthesiologists Score
DXA: Dual-energy X-ray absorptiometry scan
EQ-5D-3L: European Quality of Life – 5 dimensions – 3 levels
ITT: Intention to treat
MCID: Minimal clinically important difference
OSS: Oxford Should Score
PHF: Proximal humerus fracture
PROM: Patient-reported outcome measure
RCT: Randomized controlled trial
REDCap: Research Electronic Data Capture
SD: Standard deviations
SPIRIT: The Standard Protocol Items: Recommendations for Interventional Trials
WHO: World Health Organization
